## Abstract

**Introduction:**

Motor dysfunction, including bradykinesia, rigidity, tremor, and gait disturbance, is the core clinical feature of Parkinson’s disease (PD) and a major cause of disability. In early-stage PD (Hoehn and Yahr ≤2.5), neurodegeneration is relatively mild, and timely intervention may help preserve motor function and delay progression. Although dopaminergic medications effectively alleviate motor symptoms, their long-term use is associated with motor fluctuations and levodopa-induced dyskinesia. Acupuncture, a low-risk, well-tolerated intervention, has shown potential in improving motor performance in PD, but high-quality evidence in early-stage patients is lacking.

**Methods and analysis:**

This single-blind, sham-controlled randomized clinical trial will enroll 120 patients with early-stage PD (disease duration ≤3 years). Participants will be randomly assigned in a 1:1 ratio (*n* = 60 per group) to the true acupuncture (TA) or sham acupuncture (SA) group using stratified block randomization (block size 4) by study center. Treatment will be administered three times weekly for 12 weeks, with follow-up to 15 months. The primary outcome is the change in composite clinical motor score (CCMS) from baseline to week 12. The secondary outcomes include Movement Disorder Society unified Parkinson’s disease rating scale (MDS-UPDRS), Purdue Pegboard Test score (PPTS), Timed Up and Go Test (TUG), 6-min walk test (6MWT), Non-Motor Symptoms Scale (NMSS), 39-item Parkinson’s Disease Questionnaire (PDQ-39), Clinical Global Impression Scale (CGI), and levodopa equivalent daily dose (LEDD). Acupuncturists will not be blinded while participants, outcome assessors, and data analysts remain blinded. The primary analysis will use intention-to-treat (ITT) with mixed-effects models for longitudinal changes, handling missing data via multiple imputation by chained equations.

**Discussion:**

This study aimed to evaluate the efficacy and safety of acupuncture in improving motor function in early-stage PD. The results will help determine its potential role as an adjunctive therapy to preserve motor function.

**Clinical trial registration:**

https://itmctr.ccebtcm.org.cn/, identifier ITMCTR2025001290.

## Introduction

Parkinson’s disease (PD) is a progressive neurodegenerative disorder characterized primarily by motor dysfunction, including bradykinesia, rigidity, tremor, and postural instability, which collectively lead to progressive disability and reduced quality of life (QoL) (1). The global burden of PD is rising rapidly with population aging, affecting over 10 million people worldwide in 2020 and projected to reach approximately 17 million by 2040 (2, 3). In China, the number of patients is expected to exceed 5 million by 2030 (4), with annual new cases approaching 880,000 by 2044 (5), imposing substantial challenges on patients, families, and the healthcare system.

Early-stage PD—commonly defined as Hoehn and Yahr (H&Y) stage ≤2.5 and disease duration ≤3 years—represents a critical therapeutic window in which neurodegeneration is relatively mild and motor function can be preserved with timely intervention (6–8). Maintaining motor performance during this stage is essential, as early declines in gait, dexterity, and coordination strongly predict long-term disability (9). Dopaminergic medications, including levodopa, dopamine agonists, and monoamine oxidase-B inhibitors, remain the mainstay of motor symptom management (10). While these agents provide short-term symptomatic relief, long-term use is associated with motor fluctuations, levodopa-induced dyskinesia, and diminishing efficacy (11, 12). Moreover, pharmacological therapy alone does not halt disease progression, underscoring the need for adjunctive interventions that can sustain motor function and potentially delay the onset of treatment-related complications.

Acupuncture, an integral component of traditional Chinese medicine (TCM), is considered safe, low-cost, and well-tolerated, with a history spanning over 3,000 years in treating tremor-related disorders in China (13). Recent randomized controlled trials and meta-analyses have demonstrated that acupuncture, electroacupuncture, and scalp acupuncture significantly improve motor symptoms in PD patients (14–16). Targeted stimulation of specific acupoints (e.g., GB34 and GV16) enhances tremor control, balance, and gait performance (14, 17), while scalp acupuncture modulates cortical activity in the middle frontal gyrus and cerebellum to improve step length and walking speed (17). Mechanistically, acupuncture modulates multiple neurobiological pathways relevant to PD. In 6-hydroxydopamine (6-OHDA) rat models, 100-Hz electroacupuncture at SP6, GB34, and ST36 restores dopamine D1 receptor expression, inhibits D2 receptor overactivation, and improves motor function by regulating dopaminergic transmission (18). It also enhances neurotrophic signaling by upregulating brain-derived neurotrophic factor (BDNF) and glial cell line-derived neurotrophic factor (GDNF), promoting dopaminergic neuron survival (19, 20). Furthermore, acupuncture reduces neuroinflammation through mast cell activation and inhibition of pro-inflammatory cytokines (IL-6, TNF-α) (21), regulates GABAergic signaling to restore basal ganglia balance (22), and suppresses microglial activation and oxidative stress via the TRPC1/Ca^2+^ pathway (23). Collectively, these findings suggest that acupuncture exerts multifaceted neuroprotective effects—through dopaminergic, neurotrophic, and neuroimmune modulation, to preserve motor function and potentially delay progression in early-stage PD.

Despite these promising findings, high-quality evidence specifically targeting early-stage PD remains limited. The majority of studies have focused on patients in the mid-to-late stages of PD (14, 24, 25), leaving a gap in evidence for early acupuncture intervention. Given the potential benefits of initiating adjunctive therapy during the early stage of PD and the absence of high-quality randomized controlled trials (RCTs) focusing on motor dysfunction in this population, we designed a single-blind, sham-controlled RCT to evaluate the efficacy and safety of standardized acupuncture in improving motor performance in early-stage PD. A 12-month follow-up was incorporated to assess the sustainability of treatment effects and provide further insights into acupuncture’s role in long-term clinical decision-making.

This study aimed to evaluate the efficacy and safety of acupuncture in improving motor function in early-stage PD. The results will help determine its potential role as an adjunctive therapy to preserve motor function.

## Methods and analysis

### Study design

This is a single-blind, randomized, sham-controlled clinical trial designed to evaluate the efficacy and safety of acupuncture in treating motor dysfunction in early-stage PD. The study will be conducted at two clinical sites in Chengdu, China: the Hospital of Chengdu University of Traditional Chinese Medicine and the First People’s Hospital of Longquan District. Both institutions have well-established neurology and TCM departments, ensuring the standardized implementation of the protocol and reliable participant recruitment. The trial is scheduled to run from 21 January 2025 to 31 December 2028. Participant recruitment and interventions will take place between 1 September2025 and 1 September 2027. A detailed study flowchart is presented in Figure 1. The protocol follows the Standard Protocol Items: Recommendations for Interventional Trials (SPIRIT) 2013 Statement guidelines for clinical trial protocols (see Supplementary file 1) and is conducted in accordance with the ethical principles outlined in the Declaration of Helsinki (26). Ethical approval has been granted by the Medical Ethics Committee of the Hospital of Chengdu University of TCM (Approval No. 2025KL-020). The trial will be reported in compliance with the guidelines of the Consolidated Standards of Reporting Trials (CONSORT) (27), and it has been registered with the International Traditional Medicine Clinical Trial Registry (No. ITMCTR2025001290). A detailed schedule of enrollment, interventions, and assessments is provided in Table 1.

**Figure 1 fig1:**
[figure not shown]
Flowchart of the study design.

**Table 1 tab1:** Study schedule for data measurements.

Assessment	Study period						
Time point	Enrolment	Baseline	Treatment phase (3 months)			Follow-up (1 year)	
	Week						
	−1	0	4	8	12	38	64
Enrolment							
Eligibility screen	**×**						
Informed consent	**×**						
Randomization		**×**					
Interventions							
TA group (*n* = 52)							
SA group (*n* = 52)							
Assessments							
CCMS		**×**	**×**	**×**	**×**	**×**	**×**
MDS-UPDRS		**×**	**×**	**×**	**×**	**×**	**×**
PPTS		**×**	**×**	**×**	**×**	**×**	**×**
TUG		**×**	**×**	**×**	**×**	**×**	**×**
6MWT		**×**	**×**	**×**	**×**	**×**	**×**
NMSS		**×**	**×**	**×**	**×**	**×**	**×**
PDQ-39		**×**	**×**	**×**	**×**	**×**	**×**
CGI		**×**	**×**	**×**	**×**	**×**	**×**
LEDD		**×**	**×**	**×**	**×**	**×**	**×**
Blinding assessment					**×**		
Treatment satisfaction					**×**		
Participants safety							
AEs			**×**	**×**	**×**	**×**	**×**
Laboratory test*		**×**			**×**		**×**

*The laboratory test includes complete blood count and differential count, absolute neutrophil count, aspartate aminotransferase, alanine aminotransferase, total bilirubin, blood urea nitrogen, creatinine, albumin, coagulation test, and 12-lead electrocardiography.

TA, true acupuncture; SA, sham acupuncture; CCMS, composite clinical motor score; MDS-UPDRS, MDS unified Parkinson’s disease rating scale; PPTS, Purdue Pegboard Test score; TUG, Timed Up and Go Test; 6MWT, 6-min walk test; NMSS, Non-Motor Symptoms Scale; PDQ-39, 39-item Parkinson’s Disease Questionnaire; CGI, Clinical Global Impression Scale; LEDD, levodopa equivalent daily dose; AEs, adverse events.

### Randomization and blinding

Participants will be randomly assigned in a 1:1 ratio to either the true acupuncture (TA) group or the sham acupuncture (SA) group using stratified block randomization by study center, with a fixed block size of four. The randomization sequence will be generated by an independent statistician using SPSS version 27.0 (IBM Corp., Armonk, NY, USA), with a predetermined random seed (seed = 20,250,504) to ensure reproducibility. Group allocations will be concealed in sequentially numbered, opaque, sealed envelopes. These envelopes will be opened by designated study coordinators only after participants have been formally enrolled.

Due to the nature of acupuncture, acupuncturists cannot be blinded. However, participants, outcome assessors, and data analysts will remain blinded throughout the study. To ensure allocation concealment and prevent potential unblinding, all treatment sessions will be conducted in separate rooms. Acupuncturists will receive standardized protocol training to minimize performance bias and to avoid any inadvertent disclosure of group assignments.

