### Recruitment and informed consent

A total of 102 participants will be recruited from the neurology outpatient departments of the two participating centers. Recruitment strategies will include referrals from neurologists, announcements on hospital bulletin boards, official hospital websites, and posts via the WeChat platform. Interested individuals may contact the study coordinator by telephone, email, or in person. Initial eligibility screening will be conducted by trained neurologists, followed by detailed explanations of the study procedures. Written informed consent will be obtained from all participants prior to enrollment (see Supplementary file 2).

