### Trial status

The trial commenced in January 2025 and is currently at the stage of recruiting patients.

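### The random seed, software version, stratum and fixed block length are published while the trial recruits, so allocation concealment can no longer be assured

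*Protocol article*

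**What the plan says.** Under Randomization and blinding, the protocol article gives nearly the full recipe for the list. On the tool it says "The randomization sequence will be generated by an independent statistician using SPSS version 27.0", and it adds "with a predetermined random seed (seed = 20,250,504) to ensure reproducibility". On structure, patients are allocated 1:1 "using stratified block randomization by study center, with a fixed block size of four".

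The same section sets out the safeguards: "Group allocations will be concealed in sequentially numbered, opaque, sealed envelopes", and "These envelopes will be opened by designated study coordinators only after participants have been formally enrolled". Acupuncturists are not blinded; participants, outcome assessors and data analysts are.

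Trial status reports that the trial "is currently at the stage of recruiting patients", and Study design runs recruitment and treatment from 1 September 2025 to 1 September 2027. Nowhere does the article say that the printed seed was replaced or the list redrawn before publication.

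**The concern.** A seeded generator returns the same list every time the same script is run. That helps an audit after the trial, but during recruitment the seed has to be kept secret. Opaque envelopes and an independent statistician protect the physical list. They do not protect a list that someone else can recompute.

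A fixed, known block length adds a second and independent weakness. Staff who see the earlier allocations at their center can work out how a block must end.

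Foreknowledge of the next assignment could let someone time or select enrolments. The inclusion criteria leave room for this, since expected compliance and expected stability of medication are matters of judgement. Selection on characteristics that are not measured would not reliably be removed by the intention-to-treat analysis or by covariate adjustment. It could therefore carry through to the CCMS comparison at week 12.

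**Working it through.** The article gives no figure for predictability, so there is none to reproduce. The only related figure is the planned size, which sets the length of the list.

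**Length of the list (Sample size calculation).** With δ = 6.91, σ = 8.56, two-sided α = 0.05 and 90% power, the two-sample t-test needs 34 per group (power 0.907 at 34 and 0.898 at 33). Then 34/0.8 = 42.5, so 43; 43 × 1.2 = 51.6, so 52; the total is 104, or 104/4 = 26 blocks. The article also gives totals of 120 (Abstract; 30 blocks) and 102 (Recruitment and informed consent; 25.5 blocks, not a whole number). An outsider therefore cannot be sure of the list length.

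**What is published and what is not.**
- Published: seed, program and version, stratification factor (center, two sites), block length, ratio.
- Not published: the syntax, the generator type, the order of the centers, the number of blocks per center, the arm coding.

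The seed fixes the list only together with the unpublished items.

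**How hard the missing items are to recover.** Suppose there are M plausible scripts, one of them correct, and that wrong scripts behave like independent random lists. A block of four at 1:1 has 6 possible orders, so a wrong script matches b fully known blocks with probability 6^(−b). The chance that at least one wrong script also matches is 1 − (1 − 6^(−b))^(M−1). M is an assumption, shown over a range. The table gives the smallest b that brings this chance below 5%:

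| M (assumed) | Known blocks b | Known allocations | Chance of a false match |
|---|---|---|---|
| 10 | 3 | 12 | 0.041 |
| 100 | 5 | 20 | 0.013 |
| 1,000 | 6 | 24 | 0.021 |
| 10,000 | 7 | 28 | 0.035 |

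So 12 to 28 allocations in complete blocks would be enough, which is 12/104 = 12% to 28/104 = 27% of the planned 104. Once the right script is identified, every later assignment is known. SPSS was not run, so regeneration of this particular list was not tested.

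**Block length alone, without the seed.** Take an observer who knows every earlier allocation at the center in order, and enumerate the 6 orders of two true and two sham.
- The next assignment is certain at positions 1 and 2 never, at position 3 in 2 of 6 orders (the first two are equal), and at position 4 always: (0 + 0 + 1/3 + 1)/4 = 0.333.
- The best guess is right with probability 1/2, 2/3, 2/3 and 1 at the four positions: (1/2 + 2/3 + 2/3 + 1)/4 = 0.708, against 0.5 under unpredictable allocation.

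Over 104 assignments these ceilings are about 35 certain (104/3) and about 74 guessed correctly (104 × 0.708), against 52.

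**The case against.** A reader might infer that concealment is already lost and that anyone at a site can rerun the generator. The article does not support that. The seed does not give the list without the script, and the script is not published. The 12 to 28 allocations rest on an assumed number of candidate scripts, and the 100% figure is a ceiling that applies only after the right script has been found.

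The 33% and 71% are also ceilings. They need someone who knows all earlier allocations at that center in order, and they matter only if that person can influence enrolment. Screening is done by neurologists, who are not said to see allocations. Acupuncturists are given no part in enrolment and are trained not to disclose assignments. Envelopes are opened only after enrolment.

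Two further inferences are tempting and are not shown. The first is that the coordinators who open envelopes also handle intake. The article says "Interested individuals may contact the study coordinator by telephone, email, or in person", but it does not say that this is the same person, and being a contact point is not deciding eligibility. The second is that assessors could decode assignments. They would need the reconstructed list and each participant's center and place in the sequence, and nothing says they hold these.

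It is also fair to say that a fixed block of four is a common choice and that publishing the seed is the unusual step.

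All of this limits the size of the conclusion. It does not remove the point. The safeguards listed do not prevent recomputation, unblinded acupuncturists and the coordinators who open envelopes do know past allocations, and the article gives no sign that a fresh list is in use.

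**Conclusion.** The point holds in this form: with the seed, software version, stratum, ratio and block length public during recruitment, concealment is weakened and can no longer be assured. No misuse is alleged, and none is shown.

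The two parts differ in size. For the seed, predictability could reach 100%, on condition that the generating script is recovered; with 10 to 10,000 candidate scripts assumed, 12 to 28 known allocations would identify it. For the block length, up to 33% of assignments are certain and about 71% can be guessed, on condition that all earlier allocations at the center are known in order. In both cases selection bias in the primary result is possible, not established.

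The matter deserves correction now, because concealment cannot be restored for participants already randomized and each further enrolment from the disclosed list adds to the exposure.

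**What to change.** Have the independent statistician draw a new sequence for all participants not yet randomized, from a new undisclosed seed and with randomly varying, undisclosed block lengths within center. Then:

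- Start it at a defined point in each center, for example once the current block has been completed or formally closed. Closing a part-filled block leaves an imbalance of at most two in that center.
- Replace the unopened envelopes.
- Keep the seed and block lengths in a restricted file until recruitment ends.
- Document the switch date and report how many participants were allocated from the disclosed list. Label any comparison before and after the switch as descriptive, since splitting about 104 participants leaves little power to detect selection.

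Taking the details out of an article already published would achieve nothing, and with a new list it is unnecessary.

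If the printed seed was not the one used, a dated statement to that effect resolves the seed issue, and only the fixed, published block length remains to be changed.

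The cost is one new list, one new set of envelopes and a short amendment. No patients or visits are added.

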### Recruitment and informed consent

A total of 102 participants will be recruited from the neurology outpatient departments of the two participating centers. Recruitment strategies will include referrals from neurologists, announcements on hospital bulletin boards, official hospital websites, and posts via the WeChat platform. Interested individuals may contact the study coordinator by telephone, email, or in person. Initial eligibility screening will be conducted by trained neurologists, followed by detailed explanations of the study procedures. Written informed consent will be obtained from all participants prior to enrollment (see Supplementary file 2).

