#### Sample size calculation

As no prior acupuncture studies have reported data on the CCMS, the sample size estimation was based on a randomized controlled trial of acupuncture in PD, which reported a mean change in MDS-UPDRS Part III of −2.95 ± 0.94 in the treatment group and 3.96 ± 0.94 in the control group, yielding a between-group difference (*δ*) of −6.91 and a pooled standard deviation (*σ*) of 8.56 (Cohen’s *d* = 0.81) (15). Given that the CCMS incorporates MDS-UPDRS III (40% weight) and has demonstrated higher sensitivity and lower measurement variability compared with MDS-UPDRS III alone (37), the overall detectable effect size was expected to remain comparable, even considering potential attenuation due to the use of the Park sham needle. Therefore, *δ* = −6.91 and *σ* = 8.56 were retained for sample size estimation (Cohen’s *d* = 0.81), representing a realistic yet conservative assumption for identifying clinically meaningful motor improvement in early-stage PD. Using PASS version 21.0 (NCSS LLC, Kaysville, UT, USA) for a two-sample *t*-test, with a two-sided significance level (*α*) of 0.05 and statistical power (1 − *β*) of 90%, a total of 34 participants per group was required. Considering a 20% dropout rate, common in long-term PD trials, the adjusted sample size is 43 per group. To account for inter-center variability across the two study sites, the sample size was increased by 20% (42), resulting in 52 participants per group, totaling 104 participants.

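### The protocol gives three incompatible planned sample sizes (120, 102 and 104), and only 104 follows from its calculation as written

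*Protocol article*

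**What the plan says.** Four places in the Protocol article give a planned size:

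- **Abstract, Methods and analysis:** the trial "will enroll 120 patients with early-stage PD", split as 60 per group.
- **Recruitment and informed consent:** "A total of 102 participants will be recruited from the neurology outpatient departments of the two participating centers".
- **Sample size calculation:** a chain of steps "resulting in 52 participants per group, totaling 104 participants".
- **Table 1:** 52 in each of the two arms, which again makes 104.

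The calculation assumes a difference of 6.91 and a standard deviation of 8.56. It is made "for a two-sample *t*-test", "with a two-sided significance level (*α*) of 0.05" and 90% power. Allocation is 1:1 (Randomization and blinding), so each total splits into equal arms of 60, 51 or 52.

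**The concern.** The target size decides when enrolment ends, and the Trial status section reports that recruitment is under way, so the figure is in use now. With three published totals, closing at 102, 104 or 120 could each later be described as planned. A reader of the final report could not tell whether the trial had reached its target, fallen short or gone beyond it.

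The differing words (enroll, recruit, per group) do not resolve the conflict. If 102 people are recruited, neither 104 nor 120 can be randomized. The abstract's 60 and Table 1's 52 are both arm sizes. The abstract, which is the part most often read, carries the one figure with no derivation behind it.

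**Working it through.** **Inputs** (all from Sample size calculation): δ = 6.91, σ = 8.56, two-sided α = 0.05, power 90%, dropout 20%, center allowance 20%.

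**1. The plan's own figure.**

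- Effect size: d = 6.91/8.56 = 0.807, which the plan rounds to 0.81.
- Exact power of the two-sample t-test comes from the noncentral t distribution with 2n − 2 degrees of freedom and noncentrality δ/(σ√(2/n)). It is 0.898 at n = 33 and 0.907 at n = 34, so 34 per group is the smallest size that reaches 90%. This matches the plan.
- Dropout: 34/(1 − 0.20) = 42.5, rounded up to 43. Matches.
- Center allowance: 43 × 1.2 = 51.6, rounded up to 52. Matches.
- Total: 2 × 52 = 104. Matches the sample size section and Table 1.

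**2. Where 102 could come from.** Without rounding at the dropout step, 34/0.8 × 1.2 = 51 per group, and 2 × 51 = 102. This is a possible origin only. The section itself rounds to 43 before applying the allowance.

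**3. Where 120 could come from.** No step in the article leads to 60 per group. It exceeds the derived total by 120 − 104 = 16 participants.

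**4. Size of the disagreement.** 120 − 102 = 18 participants, and 18/120 = 15%.

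**5. Power at each total under the plan's assumptions.** Evaluable participants per arm are 80% of the arm size, rounded down to whole participants.

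| Planned total | Per arm | Evaluable per arm | Power |
|---|---|---|---|
| 102 | 51 | 40 (from 40.8) | 94.6% |
| 104 | 52 | 41 (from 41.6) | 95.1% |
| 120 | 60 | 48 | 97.5% |

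With unrounded evaluable numbers the first two become 95.0% and 95.3%. If the center allowance is taken to be fully used up, so that the evaluable number is also divided by 1.2, the effective sizes are 34.0, 34.7 and 40.0 per arm and power is 90.7%, 91.2% and 94.6%. Every total still meets 90%.

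**The case against.** The strongest defense is that nothing is wrong with the calculation. Every step reproduces, 104 is what it yields, and 102 is within two participants of that and may be a rounding variant. On this view the only real outlier is the abstract's 120, and no choice among the three endangers the trial's power. All of this stands, and it limits the point to inconsistent reporting of the target. It does not remove the point, because nothing in the article says which figure governs.

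A reader might infer more than the documents support:

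- **That the 90% power belongs to none of the totals.** It does not follow. The 90% is attached to 34 evaluable per group, and 104 is that number with two declared allowances added. Power above 90% when an allowance is not fully used is what an allowance produces.
- **That 102 must be wrong because it is not a multiple of the block size of four.** Blocks fill within each of two centers, so divisibility of the total settles nothing: 104 recruited as 53 + 51 also leaves an incomplete block at each center.
- **That the 20% center allowance is an error.** It is stated openly with a cited source that is not available here. It adds participants and harms no inference, and what to call it is a matter of wording.
- **That the ambiguity allows stopping on the results.** The article describes no interim efficacy analysis, says that participants, outcome assessors and data analysts stay blinded, and describes the monitoring committee's review in terms of safety and adherence. The loss is of a clear reference point, and there is no sign of intent.

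**Conclusion.** The point holds as an inconsistency in the planned sample size. Three current statements of the target (120, 102 and 104) cannot all be true, and they differ by up to 18 participants. Only 104 is derived as written; 102 has a plausible but unstated origin, and 120 has none.

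There is no power shortfall: power is about 94.6% to 97.5% across the three totals after 20% dropout. Those values rest on the plan's δ = 6.91 and σ = 8.56, the exact t-test, equal arms and 20% loss in each arm. A smaller true effect would lower power at every total, but that is a question about the assumed effect and does not bear on which total is the target.

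**What to change.** Confirm which total was approved, and state it identically in the abstract, the recruitment section, Table 1 and the sample size section. Use 104 (52 per group) unless 120 is the approved size. If it is, keep 120, change Table 1 and the recruitment section to match, and add the derivation that leads to 60 per group.

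If 104 is confirmed, the cost is a wording correction in two places (abstract and recruitment section), with no change to design or analysis. If 120 is confirmed, the recruitment section, Table 1 and the sample size section need editing. The correction should be made while recruitment is still open, so that the target is on record before enrolment closes.
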